### Sample size and power analysis

We propose to collect a sample of 180 participants and we estimate (based upon Hodgins et al., 2009) that we will successfully follow about 153 participants at three months. This number will ensure a heterogeneous sample of individuals that will provide a valid assessment of the perceived value of different components of the SCTs. Based upon previous experience, about half will be of each sex. This number will also provide sufficient power to conduct the proposed statistical tests comparing the two conditions, based upon gambling frequency and NODS data from Hodgins et al. (2001, 2009), assuming a correlation of .5 between baseline and follow-up values, power = 0.80 and a Bonferroni corrected α = .025 (.05/2 outcome variables). This sample size is estimated so as to be sufficient to detect a difference of about 2 gambling days per month between conditions at each follow-up interval (medium effect size). This degree of difference is clinically meaningful in terms of gambling involvement. Similarly, this sample size will detect a 1 point difference on the NODS at 12 months. Given the complexity of estimating power for HLM models, these calculations are based upon a more simple repeated measures ANOVA model [59], with an attrition rate (i.e., not followed after baseline assessment) estimated to be 15%. The proposed hlm analysis will likely have greater statistical power because all observed data are included.

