### Baseline assessment

The brief telephone baseline assessment (adapted from Hodgins et al. 2009) will include a demographic profile (age, sex, education, marital status, income, ethnicity and racial status, employment status) and a gambling, mental health and treatment history including a timeline interview of types of gambling (online, land-based), frequency, and money spent for the past three months [48,49]. Problem gambling severity will be assessed using the past year Problem Gambling Severity Index and the lifetime and past three month version of the NORC DSM-IV Screen for Gambling Problems (NODS) [50,51] which indicates DSM-IV severity. Hodgins [52] administered the NODS to problem gamblers as part of a 1-year follow-up after a brief treatment to assess its utility as a treatment outcome measure. Internal reliability was fair to good and the factor structure and item-total correlations supported the existence of a single higher order construct that correlated moderately with gambling behavior and outcome. Self-efficacy will be administered using the Gambling Abstinence Self-efficacy Scale (GASS, [53], a 21 item self-report scale with evidence of concurrent and predictive validity in problem gambling treatment samples. In addition, participants will be asked to identify a treatment goal (quit or reduce gambling) and how successful they think they would be (0 “not at all” to 10 “extremely”) in the next 6 months and in the next 12 months. The Kessler 10 (K10) questionnaire will be included to provide a continuous measure of general psychological distress that is responsive to change over time. The K10 has been well validated and its brevity and simple response format are attractive features. It also produces a summary measure indicating probability of currently experiencing an anxiety or depressive disorder [54,55]. Quality of life will be assessed by the WHOQoL-8, an eight item version of a widely used measure. This short form has been used in a number of countries, is robust psychometrically, and overall performance is strongly correlated with scores from the original WHOQoL [56].

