### Primary and secondary outcome variables

Two major outcome variables for testing the primary and secondary hypotheses will be: mean days per month gambling and NODS scores. Mean dollars lost per gambling day, total dollars lost and self-rated improvement will be used as secondary outcome variables. Days and dollars spent gambling will be calculated for the three months pre-treatment and for each follow-up period. The data will be inspected for approximate normality or symmetry and, if necessary, subjected to appropriate transformation.

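### The two primary outcomes are sized at a Bonferroni .025 with no step-down rule: valid, but Holm's procedure would give more power at the same 5% family-wise error when both outcomes respond

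*Protocol article*

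**What the plan says.** The section on primary and secondary outcome variables states: "Two major outcome variables for testing the primary and secondary hypotheses will be: mean days per month gambling and NODS scores". The section on sample size and power analysis sizes the trial for these outcomes with "a Bonferroni corrected α = .025 (.05/2 outcome variables", "assuming a correlation of .5 between baseline and follow-up values, power = 0.80". The targets given there are "a difference of about 2 gambling days per month between conditions at each follow-up interval (medium effect size" and, for severity, "this sample size will detect a 1 point difference on the NODS at 12 months". It plans 180 participants, 15% attrition, and expects that "we will successfully follow about 153 participants at three months".

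The Analyses plan section fits a separate random effects model to each outcome. It gives no alpha and no rule for combining the two primary results. No Holm, step-down or other alpha-recycling rule appears in the article. The .025 stands only in the power section.

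**The concern.** With two hypotheses, once one is rejected at .025 only one is left, and it can be tested at .05 without family-wise error exceeding 5%. If both outcomes are held at .025 throughout, that possibility is given up with no gain in family-wise error control. For example, with p = .01 for days and p = .04 for NODS, fixed Bonferroni declares only days significant, whereas Holm declares both.

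At stake is some power on each outcome and more on the joint result that frequency and severity both improve. The article plans for an effect on both outcomes, with power at 80%, so this is a setting in which a step-down rule can help.

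**Working it through.** **Inputs from the article:** two primary outcomes; alpha .025 each; power .80; baseline to follow-up correlation .5; a medium effect for days; 15% attrition; 180 randomised and about 153 followed. **Assumed, because not stated:** two-sided tests; 1:1 allocation; a medium effect means d = 0.5; NODS also has 80% power (no SD is given for its 1-point difference). The correlation ρ between the two test statistics is not given, so a range is shown.

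**Step 1. Reproduce the planned size.** With r = .5, the SD of the change score is SD × √(2(1 − .5)) = SD. Then n per arm = 2 × ((2.241 + 0.842)/0.5)² = 76.04, rounded up to 77, so 154 in total. Dividing by 0.85 gives 181.2, or 182 randomised. The article has 153 and 180, so the plan's figure reproduces. With 76.5 per arm, power at two-sided .025 is 80.3%.

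**Step 2. Power under Holm, both outcomes at their design effect.** Each test statistic has mean 2.241 + 0.842 = 3.083. Holm rejects outcome A if |Z_A| > 2.241, or if |Z_A| > 1.960 and |Z_B| > 2.241. Bivariate normal integration gives:

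| ρ | Per outcome, Bonferroni | Per outcome, Holm | Both, Bonferroni | Both, Holm | At least one, either rule |
|---|---|---|---|---|---|
| 0 | 80.0% | 85.5% | 64.0% | 75.1% | 96.0% |
| .3 | 80.0% | 85.0% | 66.6% | 76.6% | 93.4% |
| .5 | 80.0% | 84.6% | 68.7% | 77.8% | 91.3% |
| .7 | 80.0% | 84.1% | 71.3% | 79.4% | 88.7% |

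The gain per outcome is 5.5, 5.0, 4.6 and 4.1 points. It falls to 3.7 at ρ = .8 and 3.2 at ρ = .9. The gain for showing both is 8 to 11 points.

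**Step 3. Equivalent sample size.** Reaching Holm's per-outcome power under Bonferroni needs N multiplied by ((2.241 + z(power))/3.083)². That is 1.147 at ρ = 0, 1.118 at .5 and 1.104 at .7, or about 10 to 15% more participants. This too holds only with both outcomes at their design effect.

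**Step 4. Gain for an 80%-powered outcome when the other does less well.**

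| Other outcome | ρ = 0 | ρ = .3 | ρ = .5 | ρ = .7 |
|---|---|---|---|---|
| 80% power | 5.5 | 5.0 | 4.6 | 4.1 |
| 50% power | 3.5 | 2.6 | 2.0 | 1.2 |
| No effect | 0.17 | 0.17 | 0.16 | 0.10 |

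(Percentage points.) In the 50% case, the weaker outcome itself gains about 9 points for ρ from 0 to .5.

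**Step 5. Family-wise error under Holm.** With both nulls true, it is 4.9% at ρ = 0, 4.6% at .5 and 4.0% at .8. With one true null and the other outcome at its design effect, it is 4.5% at ρ = 0 and lower as ρ rises. The 5% limit holds in general: with both nulls true, Holm makes an error only if its first step, which is the Bonferroni test, rejects; with one null true, that null is never tested above .05.

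**The case against.** The strongest case against is that nothing in the plan is wrong. Bonferroni for two outcomes is valid, the stated size reproduces, and the .025 appears among planning inputs, not as a rejection rule. Sizing at .025 is compatible with Holm, whose first step is that same test, and a final multiplicity rule may sit in an analysis plan that is not shown. This stands. A reader might infer that the article commits to a fixed .025 for the final tests; it does not say so. What can be said is that the only alpha stated is the Bonferroni one.

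Three further inferences are not supported.

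- **That the gain is a general 4 to 6 points.** It is 4.1 to 5.5 points for correlations up to .7 and needs the full design effect on both outcomes. Step 4 shows how quickly it shrinks otherwise.
- **That the link between NODS and gambling makes the loss worse.** The Baseline assessment section reports that NODS "correlated moderately with gambling behavior and outcome" in an earlier follow-up study. That is a correlation of scores, not evidence of shared treatment effects, and a higher correlation between the tests reduces Holm's gain.
- **That Holm is free.** It costs no participants and no family-wise error control, but each extra rejection has p between .025 and .05, where the 97.5% interval still includes the null.

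It is also fair to object that the article nowhere requires success on both outcomes. The joint-power gain is therefore useful without being a stated aim, and power for at least one success is unaffected. Finally, Holm needs one p-value per outcome. The models have four time points, and the power section refers to each follow-up for days but to 12 months for NODS. The remedy must include that choice.

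**Conclusion.** The point holds as a low-cost efficiency improvement. A Bonferroni .025 without a step-down rule is valid and conservative; Holm is never less powerful and controls the same 5% family-wise error for any correlation. The size of the benefit depends on both outcomes responding: at the design effects it is about 4 to 5.5 points per outcome and 8 to 11 points for showing both, and it nearly vanishes for an effective outcome if the other has no effect. These figures rest on two-sided tests, 80% power for NODS as well as days, and test correlations from 0 to .7, none of which the article states. The sample size does not need to change.

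**What to change.** Keep N = 180 and the sizing at .025. In the Analyses plan or the power section, before unblinding, name one primary contrast per outcome and state that the smaller of the two p-values is tested against .025 and, if significant, the other against .05. Report 97.5% confidence intervals as simultaneous intervals, and say that they will not match Holm's decision for an outcome rejected with p between .025 and .05.

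The cost is a sentence or two, plus a decision on the contrast. Recruitment, data collection and the models are unchanged. If an unshown analysis plan already contains such a rule, it need only be cited.

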## Discussion

The goal of this proposal is to develop an evidence-based web resource to provide help to problem gamblers. There is a great deal of interest for such a resource in a variety of jurisdictions including a number of Canadian provinces.

The design has a number of limitations. Our recruitment method and telephone follow-up is designed to maximize the retention of participants in the trial (i.e., enhance the internal validity of the research). This design may limit the generalizability of the findings (i.e., external validity) as we will not assess the efficacy with individuals who are unwilling to enter a clinical trial but would who briefly visit a site and look at or use one or more tools. Future research will be required to address the issue of how effective a free online resource would be. A second limitation of the design is that we will not be able to isolate the effective ingredients of the intervention as numerous strategies are available for use. Protocols for outcome studies of face-to-face therapies ensure that adherent participants (i.e., those that attend sessions) are exposed to all active treatment components. In contrast, with self-directed treatment, these components are offered as a menu of options. “Adherent” participants (i.e., those that visit the website) may select only a few strategies. However, we will be tracking the use of the various program components so we will be able to conduct some correlational analysis of use and outcome to develop hypotheses for future research. Similarly, although we will recruit individuals who are not currently accessing treatment for gambling problems, individuals may choose to access treatment resources during the trial. In fact, as we have in previous trials, we will provide information about treatment resources to all participants. We will monitor involvement and describe this involvement at each follow-up (overall very low in previous trials).

Treatment outcome research relies on self-reported gambling behaviour. We will collect this information using standardized and validated procedures to enhance accuracy and we will also confirm using collateral reports from family and friends. Nonetheless, reliance on self-report adds variability to the data. A final limitation is the relatively brief assessment of participants. In order to minimize the potential therapeutic impact of the assessment process, we desire to keep it brief but we also want to explore potential predictors of outcome. Therefore, a number of assessment domains (e.g. comorbid mental health, social support, quality of life) are assessed using very brief instruments and the extensive data required to examine cost effectiveness will not be collected in this trial. Future, more targeted research with comprehensive instruments will be required to follow-up on positive results.

Despite these limitations, this trial has many design strengths which reinforce the importance of the results to policy-makers and treatment service administrators. Having numerous entryways into treatment and recovery and many types of treatment and treatment supports are crucial in effectively tackling this significant problem.
